#### Clinician-Administered PTSD Scale for DSM-5 – Revised

PTSD symptom severity is assessed based on the index trauma using the Dutch translation of the CAPS-5-R.^21^ The CAPS-5-R is a comprehensive 20-item clinical interview that assesses the presence and severity of the text revised version of the DSM-5 (DSM-5-TR) PTSD diagnostic criteria on an eleven-point scale. Total scores range from 0 to 200, with higher scores denoting greater symptom severity. The CAPS-5-R shows excellent reliability and good convergent and discriminant validity.^21^,^23^

#### EuroQol 5 Dimensions scale

Quality of life is assessed using the EuroQol 5 Dimensions scale (EQ-5D-5L).^24^ This scale comprises 14 items categorised into various aspects of health status rated on a three-point scale. It also includes a 0–100 Visual Analogue Scale (VAS) assessing perceived health and demographic characteristics. The resulting 5-digit index represents a health profile that can be converted into a total score. The EQ-5D-5L has excellent psychometric properties across diverse populations, conditions and settings.^24 25^

#### Mental Health Quality of Life Questionnaire

The Mental Health Quality of Life Questionnaire (MHQoL)^26^ assesses quality of life among individuals with mental health issues. The MHQoL comprises a descriptive system (the MHQoL-7D) and a VAS (MHQoL-VAS) ranging from 0 (‘worst imaginable psychological well-being’) to 10 (‘best imaginable psychological well-being’).^26^ The MHQoL-7D index score can range from 0 to 21, with higher scores indicating a higher quality of life. The MHQoL-VAS is used to record respondents’ self-assessed, overall psychological well-being. The MHQoL exhibits strong reliability and robust construct validity.^27^

#### Treatment inventory of costs in patients with psychiatric disorders

The treatment inventory of costs in patients with psychiatric disorders (TiC-P) maps the costs arising from psychosocial problems in adults.^28^ It consists of three components: general questions, questions regarding medical care utilisation and work-related questions (19 in total). The TiC-P is reliable and has satisfactory construct validity.^28^

### Secondary outcomes

To investigate trauma exposure, comorbidity, experiential avoidance, dissociation, social support, verbal memory and cortisol as predictors and/or moderators of treatment outcome, we will use the Dutch versions of the:

International Trauma Questionnaire (for complex PTSD).^29 30^Moral Injury Outcome Scale (for moral injury after a potentially morally injurious event).^31^The Hospital Anxiety and Depression Scale (for comorbid anxiety and depression).^32^Avoidance Assessment Questionnaire (for experiential avoidance).^33^Personality Inventory for DSM-5-Brief Form-Adult (for maladaptive personality traits).^34^Dissociative Symptoms Scale (for dissociative symptoms).^35 36^Crisis Support Scale (for social support and satisfaction with support).^37^California Verbal Learning Test (in Dutch: Verbal Learning and Memory Test (VLGT); for verbal memory performance).^38 39^MINI International Neuropsychiatric Interview – Simplified for DSM-5 (MINI-S; for the exclusion criteria of current psychotic disorder, severe alcohol or substance use disorder, high suicidal intent with a concrete suicide plan).^40 41^The Life Events Checklist (LEC-5; for PTEs).^42^The Adverse Childhood Events – International Questionnaire (for adverse experiences in childhood).^43^,^45^The Credibility and Expectancy Questionnaire (for patients’ confidence in the treatment and perceived treatment credibility).^46 47^

All these instruments have good psychometric properties. Furthermore, we will assess harms as recommended by the STRONG STAR consortium^48^ and hair cortisol for stress levels at baseline.

#### Treatment evaluation

To gain a better understanding of when to implement massed treatment and how to improve its application, we will carry out a qualitative assessment of participants’ experience, consisting of two parts. The first part entails open-ended questions to assess satisfaction with the therapy format and its execution. Participants will answer the questions in table 2 as part of a self-report questionnaire after their treatment has ended (at T1 for the M-TFT condition and at T2 for the S-TFT condition).

**Table 2 T2:** Topic list used in treatment evaluation

Questionnaire after treatment completion	Focus group
What was your experience of the treatment?	What was your experience of the treatment?
What do you see as the advantages of spaced therapy?	Which type (massed or spaced) of therapy do you prefer? Why?
What do you see as the disadvantages of spaced therapy?	What would be the optimal frequency of therapy for you? Why?
What do you see as the advantages of massed therapy?	What factors aided or hindered your treatment?
What do you see as the disadvantages of massed therapy?	What changes can we make to improve the quality of treatment?
For you specifically, what do you think would be the biggest difference between doing massed and spaced therapy?	On which aspects would you have liked to receive more help? On which ones less?
After the treatment, what treatment type would have been a better fit for you? Why do you think that is?	What were some things covered in therapy that were not valuable for you? What were some things covered in therapy that were particularly valuable to you?
What would have been the optimal frequency of treatment for you? Why?	Is there anything else you would like to say about the therapy and how it was given?
Is there anything else you would like to say about the therapy and how it was given?	
*For massed specifically:* what was your experience with therapy rotation?	
*For massed specifically:* what did you think about the order (i.e., PE and then EMDR) of treatments? Would you rather have had it the other way round? Why (not)?	

Note: the interview questions will be asked at T1 for M-TFT and at T2 for S-TFT. Focus groups will be held at the end of the study.

EMDR, eye movement desensitisation and reprocessing; M-TFT, massed trauma-focused treatment ; PE, prolonged exposure; S-TFT, spaced trauma-focused treatment ; T1, 7 weeks after baseline; T2, 17 weeks after baseline.

The second part consists of focus groups with several participants, discussing the prompts in table 2. At least two research team members will identify themes across the entries for each question of the interviews and focus groups. After reaching a consensus for the most applicable themes, each line of text is given a theme code. If entries are inconsistent or rater disagreement exists, they will be flagged and resolved through discussion among the raters. If necessary, a third rater will be involved. After this, a summary of findings will be written for each theme, including each subtheme and elaborated with quotes.

### Sample size calculation

The sample size calculation is based on the upper endpoint of the 95% CI for the difference in mean change scores from baseline to 9 months between M-TFT and S-TFT (adjusted for baseline) being less than the margin of seven CAPS-5 points (not the revised version). As the CAPS-5-R is backwards compatible with the CAPS-5,^22^ we drew from the extant RCT data examining evidence-based PTSD treatment using the CAPS-5. These treatments vary in their minimal change range from 7 to 10 CAPS-5 points, with an SD of 15.6 points.^13^ With a 5% significance level and 80% power, a total sample of 124 participants (62 in both conditions) is needed to detect non-inferiority when M-TFT is truly non-inferior to S-TFT using a 7-point difference on CAPS-5. The sample size was increased to 186, based on the 33% expected drop-out at the last assessment point at 9 months (figure 1).

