#### Clinical effectiveness

For the primary clinical outcome, repeated measurement analyses using linear mixed models (LMM) will be used to study changes over time in clinician-rated PTSD symptom severity as measured with the CAPS-5-R. We will assess differences in response patterns between the groups. In addition, we will test the difference between the two groups by running a customised test within the LMM at the 9-month time point and base our decision to declare non-inferiority on the corresponding 95% CI. The linear mixed model will compute estimates for missing data. In addition, disaggregated analyses of the primary outcomes will be conducted for gender and trauma background (profession-related vs other). All the analyses above will be carried out on an intent-to-treat basis.

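### The non-inferiority margin is set in CAPS-5 points, but the deciding 95% CI comes from a model of the CAPS-5-R, and the article states no link between the two scales for that test

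*Protocol article*

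**What the plan says.** The Sample size calculation section of the protocol article builds the trial on "the upper endpoint of the 95% CI for the difference in mean change scores from baseline to 9 months" between the arms, adjusted for baseline, "being less than the margin of seven CAPS-5 points (not the revised version". The power statement repeats the scale: "using a 7-point difference on CAPS-5". The treatments in the trial data used for planning "vary in their minimal change range from 7 to 10 CAPS-5 points, with an SD of 15.6 points". The reason given for using those data is "As the CAPS-5-R is backwards compatible with the CAPS-5".

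The measure actually taken is the revised instrument. Its section under Measures describes 20 items on an eleven-point scale: "Total scores range from 0 to 200, with higher scores denoting greater symptom severity". Table 1 schedules the CAPS-5-R at all five time points and does not list the CAPS-5.

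The Clinical effectiveness section fits a linear mixed model to "clinician-rated PTSD symptom severity as measured with the CAPS-5-R". A customised test at 9 months within that model, with its 95% CI, decides non-inferiority. No margin is named there.

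**The concern.** A non-inferiority decision compares a confidence limit with a margin, so the two must be in the same units. Here the only stated margin is in CAPS-5 points, while the confidence limit described is in CAPS-5-R points. The parenthesis in the sample size section shows that the authors do not regard points on the two versions as interchangeable.

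The article leaves at least two routes open: re-scoring the CAPS-5-R interview to a CAPS-5 total and using 7, or converting the margin to the 0 to 200 scale. They need not give the same answer. If the choice were made after unblinding, a positive result would be open to the charge that the threshold was chosen with the data in view. If an analyst simply carried the number 7 over, the test would be stricter than the one the trial was sized for.

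**Working it through.** **1. Scale of each element**

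| Element | Where in the article | Scale |
|---|---|---|
| Margin 7 (stated twice) | Sample size calculation | CAPS-5 |
| Minimal change 7 to 10; SD 15.6 | Sample size calculation | CAPS-5 |
| Backwards compatibility | Sample size calculation | Reason for using CAPS-5 trial data |
| Scheduled instrument | Table 1 | CAPS-5-R |
| Total 0 to 200 | CAPS-5-R section under Measures | CAPS-5-R |
| Mixed model and 9-month 95% CI | Clinical effectiveness | CAPS-5-R, no margin named |

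Every planning quantity is on one scale and the decision quantity is on the other.

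**2. Reproducing the stated sample size**

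The plan says "With a 5% significance level and 80% power, a total sample of 124 participants (62 in both conditions) is needed". With a true difference of zero,

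n per arm = 2 × [SD × (z₁₋α + z₀.₈₀) / margin]².

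At one-sided 5%: 2 × [15.6 × (1.645 + 0.842) / 7]² = 61.4, so 62 per arm and 124 in total. Taking the 33% drop-out as one third, 124 / (2/3) = 186; with 0.67 the result is 185.1, which rounds up to 186. The plan's figures are reproduced, so the sample size rests on margin and SD both in CAPS-5 points. The arithmetic is not at fault.

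**3. Converting margin and SD together**

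Suppose CAPS-5-R points = f × CAPS-5 points. The formula depends only on SD / margin, and 15.6f / 7f = 15.6 / 7. The sample size stays at 124 for any f.

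**4. Carrying 7 over unchanged (illustration only)**

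The documents give neither f nor the CAPS-5 score range, so f is an assumption and a range is shown. With 62 evaluable per arm, SD 15.6f and a true difference of zero,

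power = Φ( 7 / (15.6 f √(2/62)) − z ).

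At f = 1 the standard error is 15.6 × 0.1796 = 2.802, and 7 / 2.802 = 2.498. Power is Φ(2.498 − 1.645) = 80% at one-sided 5%, and Φ(2.498 − 1.960) = 70% for the upper limit of a two-sided 95% CI. For other values of f, divide 2.498 by f.

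| Assumed f | Converted margin (7f) | An unchanged 7 in CAPS-5 points (7/f) | Power with unchanged 7, one-sided 5% | Power with unchanged 7, two-sided 95% CI |
|---|---|---|---|---|
| 1 | 7 | 7 | 80% | 70% |
| 1.5 | 10.5 | 4.7 | 51% | 38% |
| 2 | 14 | 3.5 | 35% | 24% |
| 2.5 | 17.5 | 2.8 | 26% | 17% |
| 3 | 21 | 2.3 | 21% | 13% |

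Each power column should be read against its own first row. The gap between 80% and 70% in that row has nothing to do with scale: 62 per arm matches a one-sided 5% test, while the decision uses a 95% CI. That is a separate issue.

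**The case against.** The best defence is that the article does fix a margin, names its scale twice, and says that the revised instrument is backwards compatible. Read together, these suggest that the 9-month contrast will be judged in CAPS-5 points obtained from the CAPS-5-R interview. The article is also condensed, and a scoring algorithm is something the full protocol or the SAP would normally hold.

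Much of this stands. A workable reading exists, so a reader who infers that non-inferiority cannot be tested at all, or that there is no margin, goes further than the text supports. A reader might also infer that the trial has only 17% power. The documents do not support that either. The figure needs an assumed factor of 2.5, it needs 7 to be used on the scale the text expressly excludes, and it absorbs the separate mismatch between significance level and CI. Nor can it be said that the margin will be chosen post hoc, because the documents not shown may contain the rule. An unchanged 7 would, moreover, err towards failing to show non-inferiority, not towards a false claim of it.

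One part of the defence does not stand. Compatibility is offered as the reason for borrowing planning data; nothing says that a CAPS-5 total will be derived for the test. The point is also more than an omitted scoring detail, because the article states the margin on one scale and the deciding analysis on the other.

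**Conclusion.** The concern holds as a mismatch of units in the primary decision rule. The margin is in CAPS-5 points, the deciding CI is described in CAPS-5-R points, and the article gives no bridge for the test. It is repairable, and the stated 124 and 186 do not change on this account, provided that margin and SD are converted together and linearly.

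The size of the possible harm cannot be fixed from the documents. Under assumed factors of 1.5 to 3, an unchanged 7 would lower power from 80% to between 51% and 21% at one-sided 5%, or from about 70% to between 38% and 13% with a two-sided 95% CI. These figures assume no true difference, 62 evaluable per arm and an SD that scales with the score. They show why the link should be written down; they do not predict what the trial will do.

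**What to change.** In the Clinical effectiveness section, and in the SAP and registry entries, state one of the following before any unblinded look:

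- The 9-month non-inferiority contrast uses the CAPS-5 total derived from the CAPS-5-R by its backward-compatible scoring, with the scoring rule cited and a margin of 7 CAPS-5 points. The CAPS-5-R mixed model is kept for the trajectory analysis.
- The contrast stays on the CAPS-5-R, with a numeric margin on that scale, the conversion that produced it, and an SD on the same scale.

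The first is simpler because it keeps the margin and SD already stated. It costs one derived variable and a few lines of text, with the small drawback that the derived score is coarser than the 0 to 200 total. Neither option changes the design, and the first leaves the sample size as it is; under the second it is unchanged if the conversion is linear. Inclusion is planned to run until July 2027, so there is time to do this through the amendment route the article describes. If the full protocol or SAP already holds the rule, only the wording needs aligning.

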**Trial registration number:**

This protocol is registered at Overview of Medical Research in the Netherlands (OMON; trial register number 56960) and ClinicalTrials.gov (NCT06700590).

STRENGTHS AND LIMITATIONS OF THIS STUDYWith the inclusion of 186 participants, this randomised controlled trial (RCT) will be well-powered to establish the non-inferiority of massed trauma-focused treatment (M-TFT) compared with spaced-TFT (S-TFT).The current RCT will be conducted at five centres throughout the Netherlands, which will enrol patients with a variety of trauma backgrounds, increasing the generalisability of the findings.Assessments will be performed at five time points from baseline to 9-month follow-up, which allows for accurate investigation of the (cost-)effectiveness of the treatments over time.Elements of pragmatic, real world RCTs are present in the S-TFT condition in which multiple types of evidence-based trauma treatment are allowed, enabling a more representative comparison of M-TFT to standard clinical care.A potential limitation concerns differences between the M-TFT condition and the S-TFT condition in terms of therapist rotation, supervision frequency and the alternation of therapeutic elements.

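### The 124-patient calculation matches a one-sided 5% test, but non-inferiority is judged on a 95% CI; on that rule the stated 80% power is about 70%

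*Protocol article*

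**What the plan says.** Three places in the protocol article bear on this.

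- **Sample size calculation.** The criterion is the "upper endpoint of the 95% CI for the difference in mean change scores from baseline to 9 months", adjusted for baseline, "being less than the margin of seven CAPS-5 points (not the revised version"). The SD comes from earlier trial data, "with an SD of 15.6 points". The result follows: "With a 5% significance level and 80% power, a total sample of 124 participants (62 in both conditions) is needed to detect non-inferiority". This is raised to 186 for 33% expected drop-out at 9 months.
- **Clinical effectiveness.** The authors will test the 9-month contrast within the linear mixed model and "base our decision to declare non-inferiority on the corresponding 95% CI".
- **Strengths and limitations of this study.** With 186 participants, the trial "will be well-powered to establish the non-inferiority" of massed compared with spaced treatment.

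No section says whether the 5% level is one-sided or two-sided, and none mentions a one-sided bound or a 90% CI. No baseline-to-outcome correlation is given.

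**The concern.** A non-inferiority decision uses only one end of the interval. The upper end of an ordinary two-sided 95% CI is a one-sided 2.5% test, while a one-sided 5% test corresponds to the upper end of a 90% CI. If the sample size was computed at one level and the decision is taken at the other, the stated power does not belong to the test that will be run.

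This affects the primary clinical question. The two-sided 95% CI rule does not raise the risk of falsely declaring non-inferiority, so the loss is in power: a massed treatment that is truly as good has a larger chance of an inconclusive result than the article tells its readers. There is a second risk at analysis. If sidedness is still open when results are known, the choice between a 90% and a 95% interval could decide the conclusion and would look post hoc.

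**Working it through.** **Inputs, all from Sample size calculation unless noted.** Margin 7 CAPS-5 points; SD 15.6; power 80%; significance level 5%, sidedness not stated; 1:1 allocation (Study procedures); drop-out 33%. The true difference is not given as a number. I assume 0, the usual choice and the one that reproduces the stated figure.

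**Formula.** n per arm = 2 × (z_α + z_β)² × SD² / margin², with SD²/margin² = 243.36/49 = 4.967 and z_β = 0.842.

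**Reproducing the plan's figure (one-sided 5%, z_α = 1.645).** n = 2 × (2.486)² × 4.967 = 61.4, so 62 per arm and 124 in total. This matches exactly, with the SD of 15.6 used undiminished.

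**The rule as written (upper end of a two-sided 95% CI, z_α = 1.960).** n = 2 × (2.802)² × 4.967 = 77.96, so 78 per arm and 156 in total. This does not match the stated figure.

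**Power at 62 per arm.** The standard error is 15.6 × √(2/62) = 2.802, and 7/2.802 = 2.498.

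| Situation | Calculation | Power |
|---|---|---|
| One-sided 5%, true difference 0 | Φ(2.498 − 1.645) | 80.3% |
| Two-sided 95% CI, true difference 0 | Φ(2.498 − 1.960) = Φ(0.54) | 70.5% |
| Two-sided 95% CI, massed treatment truly 1 point worse | Φ(6/2.802 − 1.960) = Φ(0.18) | 57% |

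With the noncentral t distribution, the first two become 79.9% and 69.8%, and the required sizes become 63 and 79 per arm.

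**Drop-out.** 124/0.67 = 185.1, so the inflation to 186 is correct. For the rule as written, 156/0.67 = 232.8, or about 233 randomised.

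**Sensitivity to baseline adjustment.** Suppose 15.6 is an unadjusted SD of scores and r is the correlation between baseline and 9 months. The residual SD is then 15.6 × √(1 − r²). Power at 62 per arm under the two-sided 95% CI is:

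| r | Power |
|---|---|
| 0.3 | 75% |
| 0.4 | 78% |
| 0.5 | 82% |
| 0.6 | 88% |

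Reaching 80% needs a residual SD of 7 / [(1.960 + 0.842) × √(2/62)] = 13.9, which means r of about 0.45. These values of r are assumptions; the article gives none.

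**The case against.** There are four serious counter-arguments.

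1. **The text may mean a one-sided 95% upper limit.** Pairing an upper endpoint with a 5% level would then be coherent, and 124 would give 80.3% power. The one-sided 5% level is also my inference from the number 62; the article does not state it. This reading cannot be excluded, but the article never says it, and an analyst asked for the 95% CI of a mixed-model contrast would ordinarily produce the two-sided interval. If this is what was meant, both sections still need to say so.

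2. **The comparison is adjusted for baseline, so 70% may be too low.** The table above shows the range for a raw score SD. If 15.6 is instead the SD of change scores, and the baseline and 9-month SDs are equal, the residual SD is 15.6 × √((1 + r)/2). Power is then 87% at r = 0.3, 82% at r = 0.5 and 77% at r = 0.7. If the baseline SD is only 0.7 of the 9-month SD, power is 73% to 77% for r between 0.3 and 0.5. What stands is that the true power could lie above 80%. What does not follow is that the stated 80% rests on adjustment, because 124 comes out with no variance reduction at all.

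3. **The mixed model uses earlier visits from patients lost by 9 months.** It may recover some information, so 70% and 233 are on the cautious side. The article's own calculation nevertheless sizes the trial on the 124 who remain. Power of about 86% would require all 186 to be evaluable, which contradicts its drop-out assumption.

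4. **Nothing in the design has to change.** That is true, and it bears on the cost of the correction, not on whether the stated figure is right.

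**Conclusion.** The concern holds: the passage is wrong as written. On the article's own margin and SD, the sample size corresponds to a one-sided 5% test, while the decision rule on its ordinary reading is a one-sided 2.5% test. The power for that rule is 70.5% (69.8% by t), about 10 percentage points below the stated 80%, and 80% would need 156 evaluable patients instead of 124.

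The size rests on three assumptions: a true difference of zero, 62 evaluable patients per arm, and an SD of 15.6 with no further reduction from baseline adjustment. The mismatch in error rates depends on none of the unstated correlations. It disappears only if the 95% CI was meant as a one-sided bound, which the article does not say.

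**What to change.** Keep 186 patients and the two-sided 95% CI. Then:

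- In Sample size calculation, say that the interval is two-sided (one-sided level 2.5%), and restate the power as about 70% for 124 evaluable patients at SD 15.6 with no variance reduction.
- If a one-sided 95% upper limit was intended, say so there and in Clinical effectiveness: one-sided 5%, equal to the upper end of the two-sided 90% CI. The figure of 124 for 80% power can then stay.
- State whether 15.6 is a raw, change-score or baseline-adjusted SD. Give the baseline-adjusted power beside the unadjusted figure, with the correlation assumed and its source.
- Soften the claim in Strengths and limitations so that it agrees with the power that results.

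The cost is wording in the protocol and analysis plan, and a less favourable stated figure if the two-sided interval is kept. No extra patients are needed. Inclusion is planned to run until July 2027, so sidedness can be fixed on record before the 9-month comparison is made.
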